### Measurements

Four time points (baseline, 3, 12 and 24 months) will be used for data collection of the primary and secondary outcomes using an online questionnaire. Baseline measurement will be conducted face-to-face and follow-up measurements preferably through online communication, e.g. Skype or FaceTime. When follow-up measurements through online communication are not possible, follow-up measurements will be conducted face-to-face. At all four time points participants will receive an accelerometer (Activ8) for the objective measurement of physical activity. Participants will be instructed to wear the Activ8 for five consecutive weeks at baseline and eight consecutive days at all following time points, except during sleeping, showering, bathing or swimming. For the economic evaluation, patients will be asked to complete eight retrospective 3-monthly online cost questionnaires. All of these questionnaires will have a 3-month recall period to cover the full duration of follow-up (i.e. 24 months). No financial incentives to complete questionnaires or to wear accelerometers will be offered. Table 2 gives a summary of all outcome measures and time points.

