### Other measures

*Patient characteristics,* i.e. age, gender, educational level, profession, employment status, and medical history related to LBP over the past 2 years, are measured using an online questionnaire. Besides that, relevant clinical variables such as duration of current complaints, Body Mass Index, past surgeries, risk of developing persistent LBP, the presence of central sensitivity, and possible co-morbidities are collected.

*Content and number of physiotherapy sessions* are measured trough registration forms, developed by the researchers. The registration forms collect information on the number and content of face-to-face sessions, adherence to face-to-face sessions and deviations from the study protocol and are completed by the physiotherapists.

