#### Effectiveness

The primary purpose of this study is to estimate the effectiveness of e-Exercise LBP for improving physical functioning compared to usual primary care physiotherapy in patients with LBP. The primary analysis time point for the study will be 12 months following baseline, however 3- and 24-month changes will also be evaluated. To evaluate the overall effectiveness of e-Exercise LBP, differences in change scores per group and time period will be estimated on primary and secondary outcomes using linear mixed models (LMM) with random effects to control for correlation within patients and physiotherapists [70, 71]. The three-level hierarchy will exist of repeated measurements (level 1), nested within patients (level 2), nested within physiotherapists (level 3). Analysis will be controlled for baseline variables that have been shown to be related to physical functioning, e.g. age, gender, pain severity scores, duration of pain [72–74].

In addition, a per-protocol analysis that only includes patients of the intervention group which were adherent to the smartphone application and the entire usual care group will be performed. Patients will be considered to be adherent to the smartphone application if they used the application for at least 2/3rd of the duration (i.e. 2 out of 3 week for the “low-risk” profile and 8 out of 12 weeks for the “medium- and high-risk” profile) [35, 75]. Per-protocol analyses will be performed using LMM with the same 3-level structure, and will be controlled for the same variables as the primary analysis.

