##### Identification, measurement and valuation of costs

When the societal perspective is applied intervention, healthcare, informal care, unpaid productivity, and paid productivity costs will be included. When the healthcare perspective is applied, only costs accruing to the formal Dutch healthcare sector will be included. The costs of e-Exercise LBP will be estimated using a bottom-up micro-costing approach [76]. Information on the patients’ other kinds of resource use will be collected using eight 3-monthly retrospective cost questionnaires with 3-month recall periods. Healthcare utilization, unpaid productivity, and informal care will be valued in accordance with the “Dutch Manual of Costing” [77]. Paid productivity losses comprise of absenteeism (i.e. sickness absence) and presenteeism (i.e. reduced productivity while at work). Absenteeism was measured using a modified version of the IMTA Productivity Cost Questionnaire (iPCQ). Absenteeism will be valued in accordance with the “Friction Cost Approach” (FCA), using gender-specific price weights [78, 79]. Presenteeism will be measured using the “World Health Organization – Work Performance Questionnaire” as well as the “Productivity and Disease Questionnaire”, and valued using gender-specific price weights as well [78–81].

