##### Statistical analyses

Missing cost and effect data will be imputed using ‘Multivariate Imputation by Chained Equations’ and the results will be pooled using Rubin’s rules [87]. Cost differences (∆C) and effect differences (∆E) will be estimated using LMM, and will be corrected for the same baseline variables as the effectiveness analysis. To account for the highly skewed nature of cost data, bias-corrected and accelerated bootstrapping with 5000 replications will be used to estimate 95% confidence intervals around the cost differences (∆C). Incremental cost-effectiveness ratios (ICERs) will be calculated by dividing the difference in costs by the difference in effects (∆C/∆E). Uncertainty surrounding the ICERs will be graphically illustrated by plotting bootstrapped cost-effect pairs on cost-effectiveness planes and by estimating cost-effectiveness acceptability curves. To test the robustness of the study results, several sensitivity analyses will be performed [88].

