Because the study design is well-considered, several potential operational issues are taken into account. An important operational issue is the physiotherapists’ training in the e-Exercise LBP intervention. From previous studies we learned that implementing a blended intervention into daily routine is a complex process that changes existing routines [28]. Therefore, training of the participating physiotherapists in the e-Exercise LBP intervention has been expanded from a 4-h training session to two 4-h training sessions. Additionally, Siilo, a secure messenger for healthcare professionals to communicate and share information, will be used during the study to be able to provide direct assistance to participating physiotherapists. And finally, instruction videos were created to support physiotherapists in using the e-Exercise LBP intervention. Another important operational issue is the possible increased risk of drop-outs during this study due to the 24-month follow-up period and the 11 questionnaires that have to be completed during this period. To minimize this risk, a researcher (TK or RA) will conduct the follow-up assessments at 3, 12 and 24 months in person, i.e. by phone, Skype or face-to-face. A final operational issue is the belief that e-Exercise LBP will not provide a solution for all patients having LBP, nor for all physiotherapists treating patients with LBP. Therefore, selection bias could occur, e.g. participants or physiotherapists having low digital literacy skills, or have a more negative attitude towards technology in general, are less likely to be included in this study.

However, with respect to our digitalized society it is expected that the majority of patients with LBP can benefit from the e-Exercise LBP intervention. The results of this study will help to understand whether blended physiotherapy for patients with LBP can be implemented on this basis.

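### The cost difference is adjusted only for predictors of physical functioning and no baseline cost questionnaire is described, so imbalance in cost predictors is at best partly adjusted

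*Protocol article*

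**What the plan says.** In the protocol article, Measurements states that "patients will be asked to complete eight retrospective 3-monthly online cost questionnaires", and continues: "All of these questionnaires will have a 3-month recall period to cover the full duration of follow-up (i.e. 24 months". The section on identification, measurement and valuation of costs names the same source for all resource use other than the intervention itself: "eight 3-monthly retrospective cost questionnaires with 3-month recall periods". The Discussion mentions "the 11 questionnaires that have to be completed during this period" and says that a researcher "will conduct the follow-up assessments at 3, 12 and 24 months in person".

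For the analysis, the Statistical analyses part of the economic evaluation says that cost and effect differences "will be corrected for the same baseline variables as the effectiveness analysis". The rule for choosing those variables stands under Effectiveness: "Analysis will be controlled for baseline variables that have been shown to be related to physical functioning". Age, gender, pain severity and duration of pain follow as examples.

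Other measures lists what else is recorded per patient: "age, gender, educational level, profession, employment status, and medical history related to LBP over the past 2 years". Past surgeries, risk of persistent pain and co-morbidities are also collected.

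**The concern.** Costs are skewed and imprecise, and the cost difference is the numerator of every ICER. Baseline variables that predict cost are the cheapest way to gain precision and to limit the effect of arms that differ at the start. The plan instead borrows covariates selected for another outcome.

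The mismatch is plainest for the societal perspective, which includes paid productivity losses. Only a patient in paid work can incur them, yet employment status enters the cost model only if it happens to count as a predictor of physical functioning. The same holds for earlier back-pain care. The Discussion expects the benefit to appear in care use and sickness absence, and the text describes no pre-enrolment value for either.

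Two features of the design add to this. Under Study procedure, practices are allocated and their physiotherapists trained, and practice staff then approach patients, so the arms can differ in who enrols for reasons other than chance. Under Statistical analysis, missing costs are imputed as missing at random given baseline confounders. If the cost predictors are absent from that set, the imputation loses them too.

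**Working it through.** **1. Coverage of the cost questionnaires.** 8 questionnaires x 3 months = 24 months, the follow-up period the plan names. That leaves 24 - 24 = 0 months before enrolment. The Discussion's count agrees: 8 cost questionnaires + 3 follow-up assessments (3, 12 and 24 months) = 11. The text therefore describes no cost questionnaire at baseline.

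**2. Covariates.**

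| Baseline variable | Collected | Named as an example for the effectiveness model, and so for the cost model |
|---|---|---|
| Age, gender, pain severity, pain duration | yes | yes |
| Employment status | yes | no |
| Two-year back-pain history | yes | no |
| Past surgeries, co-morbidities | yes | no |
| Cost in the 3 months before enrolment | not described | no |

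**3. Inputs for the size.** From Sample size calculation: SD 14.5, difference 6, power 80%, two-sided alpha 0.05, cluster size 5, intracluster correlation 0.05, correlation 0.5, N = 165 before and 207 after 20% dropout. The plan's figures reproduce:
- unadjusted n per arm = 2 x (14.5 x (1.960 + 0.842) / 6)^2 = 91.68
- design effect = 1 + (5 - 1) x 0.05 = 1.2
- total = 2 x 91.68 x 1.2 x (1 - 0.5^2) = 165.02, against 165 stated
- with dropout, 165 / 0.8 = 206.25, so 207 as stated

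**4. Chance imbalance in a baseline cost predictor**, in SD units, with two equal arms and the ODI's intracluster correlation borrowed for costs (assumption):
- SD of the between-arm difference = sqrt(4/207 x 1.2) = 0.152
- 95% range = 1.96 x 0.152 = +/-0.30 SD

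If the predictor correlates r with follow-up cost, the part carried into the cost difference is r times this. The article gives no r, so a range is assumed:

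| Assumed r | Carried into the cost difference (95% range) | Residual variance after adjustment, 1 - r^2 | Reduction |
|---|---|---|---|
| 0.2 | +/-0.06 SD | 0.96 | 4% |
| 0.3 | +/-0.09 SD | 0.91 | 9% |
| 0.5 | +/-0.15 SD | 0.75 | 25% |

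At r = 0.5, an intracluster correlation of 0.01 to 0.10 moves the range only from +/-0.14 to +/-0.16 SD. All of these are upper figures, because the planned covariates already remove part of the imbalance.

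**5. Paid work.** If 50% to 80% of patients are in paid work (assumed), the SD of the between-arm difference in that proportion is sqrt(0.5 x 0.5) x 0.152 = 7.6 percentage points, down to sqrt(0.8 x 0.2) x 0.152 = 6.1 points. A gap of at least 10 points in either direction then arises by chance in about 19% (10/7.6 = 1.3 SD) to 10% (10/6.1 = 1.6 SD) of such trials.

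**The case against.** The strongest reply is that this is a condensed article. Its covariate list is open, the exact cost model and the sensitivity analyses may be set out elsewhere, and Table 2, to which Measurements refers the reader, is not visible. A baseline work or care-use item cannot be ruled out. This stands, and it limits the point to what the text fixes. The text does fix a rule: the cost model takes the effectiveness covariates, and those are chosen for physical functioning. An open list under that rule may let employment status in but does not require it.

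A reader might infer more than the article supports:

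- **That costs cannot be adjusted for prior care or work.** They can in part. Employment status, two-year back-pain history, past surgeries and co-morbidities are collected.
- **That every imbalance passes into the ICER.** It does not. Age, gender, pain severity and pain duration are adjusted for, and only what they leave unexplained remains.
- **That the ICER is biased by chance imbalance.** Under randomisation, chance imbalance costs precision, which the bootstrap intervals and acceptability curves express. Bias needs systematic differences. Recruitment after allocation makes these possible, but the article does not show that they occur.
- **That few practices are randomised.** No number is given, and 207 / 5 implies about 41 clusters.

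It is also fair to say that cost accumulates over follow-up and, unlike the ODI, is not a state that must have a baseline value. Finally, a baseline questionnaire may come too late: the Abstract describes 208 patients in the past tense, although Timeline leaves enrolment open until January 2020.

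**Conclusion.** The point holds in a limited form. No baseline cost questionnaire is described, and the cost difference is adjusted by a rule aimed at physical functioning. Imbalance in paid work and earlier back-pain care is therefore at best partly adjusted, and some precision of the cost difference is given up.

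The gain from adjusting for a baseline cost measure is about 4% to 25% of residual cost variance at an assumed correlation of 0.2 to 0.5. In interval width this is roughly 2% (1 - sqrt(0.96)) to 13% (1 - sqrt(0.75)). These are upper figures. What the variables already collected would recover cannot be derived from the article, which does not say how much care use the two-year history records. A systematic difference from recruitment after allocation would come on top, and its size cannot be derived either.

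This is a modest improvement to the economic evaluation. It does not affect the primary endpoint or the sample size. It is worth making because the main step uses data already in hand.

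**What to change.** **In the economic Statistical analyses section**, separate the cost model from the effect model. Suggested wording: *Cost differences will be adjusted for the covariates of the effectiveness analysis and, in addition, for employment status at baseline and the two-year history of back complaints. These variables will also be included in the imputation model for costs.* Set this down before the 12-month cost-effectiveness analysis, which Timeline places in January 2021. No new data are needed; the cost is a small number of additional model terms.

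**Only if enrolment is still open and Table 2 shows no baseline cost item**, give the existing 3-month-recall cost questionnaire once at the face-to-face baseline visit in both arms, and adjust for it. Coverage becomes 9 x 3 = 27 months, 3 before and 24 after enrolment. The cost is added patient burden, and the Discussion already names the number of questionnaires as a dropout risk. Patients enrolled earlier would have no such value, so the two covariates above should stay in the model for everyone.

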**Table 2 Tab2:**
[figure not shown]
Schedule of enrolment, interventions, and assessments

Indicator for a period; duration of the period is not limited to length of the indicator and dependent on duration of interventions and use of smartphone application

*LBP* Low back pain, *BMI* Body Mass Index, *ODI* Oswestry Disability Index, *NRS* Numeric Rating Scale, *EARS* Exercise Adherence Rating Scale, *PT* Physiotherapist, *EXAS* Exercise Adherence Scale, *FABQ* Fear-Avoidance Beliefs Questionnaire, *PCS* Pain Catastrophizing Scale, *GSE scale* General Self-efficacy Scale, *PAM* Patient Activation Measure, *EQ-5D-5L* EuroQol 5D

### Primary outcome measure

The primary outcome measure is *physical functioning* and is derived from the internationally accepted “Core Outcome Set” (COS) for research into patients with non-specific LBP. The other recommended outcomes are included as secondary parameters, i.e. pain intensity, health-related quality of life, psychological functioning and pain interference [43–45] (Table 2). All selected measurement instruments in the current study are determined to be valid and reliable in previous research.

*Physical functioning* due to pain in LBP patients is assessed by the Oswestry Disability Index (ODI), version 2.1a [44–46].

### Secondary outcome measures

*Pain intensity* is measured with an 11-point Numeric Rating Scale (NRS) for the average LBP intensity in the last week [44, 45, 47].

*Physical activity* is objectively measured using a 3-axial accelerometer, the Activ8 (ACTIV8, Valkenswaard, The Netherlands) [48]. The Activ8 is a valid instrument to detect sedentary behaviour (combination of lying and sitting), standing, walking, running, and cycling. Additionally, MET-values are given. The Activ8 measures with 12.5 Hz, an epoch of 1 s a sample interval of 5 s. Every 5 min a summary is stored of the different postures and MET-values [49]. In addition, participants are requested to fill out a short activity diary about unusual activities and reasons for device removal.

*Patient self-reported adherence to prescribed home exercises* is measured by the Exercise Adherence Rating Scale (EARS). Besides that, the EARS measures the exercise prescription and the reasons for (non-) adherence [50].

*Physiotherapist based assessment of adherence to prescribed home exercises* is measured by the Exercise Adherence Scale (EXAS). The EXAS is an interview-based questionnaire which is used by the physiotherapist during face-to-face care to determine both the qualitative performance of the recommended home exercises and the agreement between recommended home exercises and patient reported adherence [51].

*Adherence to the smartphone application* is measured in the experimental group only by means of quantitative data about usage (e.g. completed modules). The data is automatically stored on the backend of the smartphone application.

*Fear avoidance beliefs about physical activity and work is* measured using the Fear-Avoidance Beliefs Questionnaire (FABQ). The FABQ assesses the fear of movement/(re)injury and consists of items related to physical activity and work [52].

*Pain catastrophizing* is measured by the Pain Catastrophizing Scale (PCS) The PCS is a self-report measurement tool that provided a valid index of catastrophizing in clinical and non-clinical populations [53, 54].

*Self-efficacy*, i.e. the patients beliefs in their efficacy to influence events that affect their lives [55], is measured using the General Self-efficacy Scale (GSE Scale) [56–58].

*Patient activation is* assessed by the Dutch version of the short form Patient Activation Measure (PAM 13-Dutch) [59, 60]. The Pam 13-Dutch assesses patient (or consumer) self-reported knowledge, skills and confidence for self-management of one’s health or chronic condition.

*The number of recurrent LBP episodes* is measured by the number of self-reported LBP episodes during the follow-up period. A recurrent LBP episode is defined as return of LBP with a minimum duration of 24 h after a period of at least 4 weeks without pain [61].

### Other measures

*Patient characteristics,* i.e. age, gender, educational level, profession, employment status, and medical history related to LBP over the past 2 years, are measured using an online questionnaire. Besides that, relevant clinical variables such as duration of current complaints, Body Mass Index, past surgeries, risk of developing persistent LBP, the presence of central sensitivity, and possible co-morbidities are collected.

*Content and number of physiotherapy sessions* are measured trough registration forms, developed by the researchers. The registration forms collect information on the number and content of face-to-face sessions, adherence to face-to-face sessions and deviations from the study protocol and are completed by the physiotherapists.

### Sample size calculation

The required sample size was calculated according to the recommendations of Campbell et al. (2010) for cluster randomized trials [62, 63], taking into account repeated measures of the primary outcome measure physical functioning on the ODI during follow-up [64]. An intracluster correlation coefficient of 0.05 was used [65, 66]. Additionally, to detect a clinical relevant difference between groups at 12 months following baseline, a difference of > 6 points in physical functioning on the ODI [67, 68] and a standard deviation of 14.5 [69] were used in the sample size calculation. For the repeated measures of physical functioning on the ODI a correlation of 0.5 is estimated between baseline and follow-up measurements until 12 months follow-up [64]. Based on these assumptions (using a power of 80% and α = 0.05) and average cluster size of 5, in total 165 patients are needed. With an expected dropout rate of 20% a total of 207 participating patients (104 patients per arm) are needed.

### Statistical analysis

Descriptive statistics (e.g. means and proportions) will be used to explore baseline comparability. To investigate selective attrition, general characteristics and primary baseline variables of dropouts and non-dropouts will be compared All analyses will be performed according to the ‘intention-to-treat’ principle. Missing data for all outcomes and cost measures will be imputed using ‘Multivariate Imputation by Chained Equations’ under the assumption that data are missing at random given baseline confounders. For all analysis, a two-tailed significance level of *p* < 0.05 is considered to be statistically significant. All analyses will be carried out using IBM SPSS Statistics version 24.0 (Amork, New York, USA).

#### Effectiveness

The primary purpose of this study is to estimate the effectiveness of e-Exercise LBP for improving physical functioning compared to usual primary care physiotherapy in patients with LBP. The primary analysis time point for the study will be 12 months following baseline, however 3- and 24-month changes will also be evaluated. To evaluate the overall effectiveness of e-Exercise LBP, differences in change scores per group and time period will be estimated on primary and secondary outcomes using linear mixed models (LMM) with random effects to control for correlation within patients and physiotherapists [70, 71]. The three-level hierarchy will exist of repeated measurements (level 1), nested within patients (level 2), nested within physiotherapists (level 3). Analysis will be controlled for baseline variables that have been shown to be related to physical functioning, e.g. age, gender, pain severity scores, duration of pain [72–74].

In addition, a per-protocol analysis that only includes patients of the intervention group which were adherent to the smartphone application and the entire usual care group will be performed. Patients will be considered to be adherent to the smartphone application if they used the application for at least 2/3rd of the duration (i.e. 2 out of 3 week for the “low-risk” profile and 8 out of 12 weeks for the “medium- and high-risk” profile) [35, 75]. Per-protocol analyses will be performed using LMM with the same 3-level structure, and will be controlled for the same variables as the primary analysis.

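### The 165/207 sample size needs a variance factor of 0.75, but the change-score analysis as described does not secure it; without baseline ODI in the model, power could fall to about 68%

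*Protocol article*

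**What the plan says.** The Sample size calculation section targets "a difference of > 6 points in physical functioning on the ODI" at 12 months, with "a standard deviation of 14.5". On clustering it states: "An intracluster correlation coefficient of 0.05 was used", with an average cluster size of 5. Error rates are given as "using a power of 80% and α = 0.05", and the Statistical analysis section makes the test two-sided ("For all analysis, a two-tailed significance level of" p < 0.05). The section says that repeated ODI measurements were allowed for, and that "a correlation of 0.5 is estimated between baseline and follow-up measurements until 12 months follow-up". It arrives at 165 patients, and at 207 after 20% dropout. It does not print the variance factor that the correlation produces.

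The Effectiveness section makes 12 months the primary time point and says that "differences in change scores per group and time period will be estimated on primary and secondary outcomes using linear mixed models". The model has three levels: measurements within patients within physiotherapists. It controls for baseline variables "related to physical functioning, e.g. age, gender, pain severity scores, duration of pain". Baseline ODI is neither named nor excluded. The section does not say whether the baseline measurement enters as an outcome row, as a covariate, or with a mean held common to both arms.

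**The concern.** The sample size takes credit for a 25% reduction in variance. Whether the primary analysis earns it depends on how baseline ODI is handled. A model that adjusts for baseline ODI has residual variance factor 1 - r². An unadjusted change score has factor 2(1 - r). At r = 0.5 these are 0.75 and 1.00, so the unadjusted change score is no more precise than follow-up scores alone.

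The text describes change scores and leaves baseline ODI out of its examples. An analyst who follows it literally, with baseline as a first-level row and free means by group and time, obtains with complete data the simple difference in change at 12 months. That analysis does not have the power claimed for the trial. Its estimate also depends on any chance difference between arms in baseline ODI.

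**Working it through.** **Inputs** (Sample size calculation, except sidedness, which is in Statistical analysis): difference 6; SD 14.5; two-sided alpha 0.05 (z = 1.960); power 80% (z = 0.842); ICC 0.05; cluster size 5; baseline to follow-up correlation r = 0.5; dropout 20%.

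**1. Reproducing the plan's figure**

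- Per arm, no clustering: 2 × (1.960 + 0.842)² × 14.5² / 6² = 91.68, so 183.36 in total.
- Design effect: 1 + (5 - 1) × 0.05 = 1.20, giving 183.36 × 1.20 = 220.03.
- Times 0.75: 165.02, the stated 165.
- Dropout: 165 / 0.80 = 206.25, rounded up to the stated 207.

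Without the factor 0.75 the total is about 220, so the plan must have used it.

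**2. Where 0.75 can come from**

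- Baseline adjustment, one follow-up: 1 - 0.5² = 0.75.
- Mean of two follow-ups, no baseline: (1 + 0.5)/2 = 0.75.
- Mean of two follow-ups minus baseline: 1 + (1 + 0.5)/2 - 2 × 0.5 = 0.75.

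The last two require r = 0.5 between follow-ups as well. The first is the most natural, because the article describes the 0.5 as a correlation with baseline and the target is a difference at one time point.

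**3. Power at 165 evaluable (82.5 per arm)**

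SE = 14.5 × √(2 × design effect × factor / 82.5); power = Φ(6/SE - 1.96).

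| Analysis at 12 months | Factor | Design effect | SE | Power |
|---|---|---|---|---|
| Baseline ODI adjusted | 0.75 | 1.20 | 2.142 | 80.0% |
| Change score, unadjusted | 1.00 | 1.20 | 2.473 | 67.9% |
| Change score, covariates explain 10% | 0.90 | 1.20 | 2.346 | 72.5% |
| Change score, covariates explain 20% | 0.80 | 1.20 | 2.212 | 77.4% |
| Change score, ICC 0.025 | 1.00 | 1.10 | 2.368 | 71.7% |
| Change score, ICC 0 | 1.00 | 1.00 | 2.258 | 75.7% |

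For 80% power, the unadjusted change score at ICC 0.05 needs about 220 to 221 evaluable patients: 220/0.80 = 275 enrolled, or 221/0.80 = 276.25, rounded up to 277.

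**4. Sensitivity to the correlation** (165 evaluable, ICC 0.05): at r = 0.4 the change score has 60.1% power and the baseline-adjusted analysis 75.4%; at r = 0.6 the figures are 77.4% and 85.8%.

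**5. Chance imbalance.** With r = 0.5 and equal SDs, the regression slope on baseline is 0.5, whereas a change score subtracts the whole baseline difference. The unadjusted estimate therefore moves by half of any baseline difference. As an illustration, a 3-point difference moves it 0.5 × 3 = 1.5 points, a quarter of the 6-point target.

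**The case against.** The best reply is that the article does not commit to an unadjusted change score. The covariate list is introduced as examples, and baseline physical functioning plausibly meets the stated rule of being related to the outcome. A change-score model with baseline ODI as a covariate gives the same treatment effect and standard error as an analysis of follow-up ODI adjusted for baseline, and keeps 80%. A condensed article may also leave the full covariate list to an analysis plan that is not shown. This stands in part: it makes the loss of power conditional. It does not make the text adequate, because the article affirmatively describes a change-score comparison and omits from its examples the variable on which its sample size most plausibly relies.

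A second reply is that 0.75 may come from averaging the 3- and 12-month scores. That is possible, but it does not reconcile the two sections. The primary time point is 12 months alone, and an unadjusted 12-month contrast, whether of follow-up scores or of change, again has factor 1.00.

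Third, 68% assumes no gain from other covariates and an ICC of 0.05 carried unchanged to the change score. A stable cluster effect would cancel in a change score. Favourable assumptions can also combine: ICC 0 with covariates explaining 10% gives 0.90 × 1.00 = 0.90, equal to 0.75 × 1.20, which just restores 80%. This stands. The article supplies neither quantity, so such a recovery cannot be counted on.

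A reader might also infer that few clusters, with patients recruited through practices already allocated, make the change-score contrast biased and that baseline adjustment cures it. The document does not support this. At its own figures 207/5 is about 41 clusters. Chance imbalance does not bias a change score in expectation; it affects precision and the estimate in the trial at hand. If recruitment differed systematically between arms, baseline adjustment would not guarantee a cure.

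**Conclusion.** The point holds in conditional form. That the plan needs a factor of 0.75 to reach 165 and 207 is a matter of arithmetic. That the factor comes from baseline adjustment is an inference, though the most natural one. The described 12-month change-score analysis secures that factor only if baseline ODI is adjusted for or baseline means are constrained to be equal, and the article specifies neither.

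If neither is done, power at 165 could be about 68% (r = 0.5, ICC 0.05 on the change score, no gain from other covariates). More favourable single assumptions give about 72% to 77%. A reader might conclude that the trial's power simply is 68%; the open covariate list does not support that.

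**What to change.** In the Effectiveness section, specify the primary model in one of two ways: follow-up ODI as the outcome with baseline ODI named as a covariate, or a mixed model that includes the baseline measurement with its mean constrained to be equal across arms. State that the primary result is the between-arm contrast at 12 months. The per-protocol analysis takes the same covariates and needs no separate change.

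In the Sample size calculation section, print the variance factor and its source. If it came from averaging follow-ups, say so and reconcile it with the single 12-month primary time point.

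The cost is a few sentences of plan wording, settled before outcomes are compared by arm. No patients and no data are added. The analysis then matches the factor that reproduces 165, and the estimate no longer depends on chance imbalance in baseline ODI, as far as a linear adjustment captures it.
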